### Study Outcomes

#### Primary Outcomes

The primary outcome will be measured as the average percentage of patient compliance with preoperative recommendations (the number of recommendations met by surgical intervention). Compliance with type 2 recommendations will be checked at the point of anesthesia consultation, whereas types 1 and 3 at the point of patient reception and preparation the day of surgery.

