#### Exclusion Criteria

Patients with two scheduled operations during the same clinical episode or time period will be excluded from the study. Nonautonomous patients, whose caregivers cannot be located when personal preoperative recommendations (Multimedia Appendix 2) are provided, and patients of the intervention group who have not downloaded and registered on Listeo+ will also be excluded. To avoid the loss of patients, a rescue procedure will be used with patients who, within 7-14 days, have not registered on the Listeo+ app. A telephone call will be made urging them to register on the Listeo+ app. If a patient has not registered within 72 hours (3 days) after the rescue call has been made, he or she will be excluded from the study.

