### Participants

Figure 1 presents the patient flow from the MAS assessment appointment to hospital discharge. This includes a first visit to surgery consultation, a second face-to-face anesthesia consultation (all patients except for ophthalmological patients with indication for topical anesthesia), and a third hospitalization visit to undergo MAS. Patients in the control group will follow the existing MAS patient assistance route in the centers, which consists of providing written recommendations. Participants are not going to pay for the app.

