**Figure 3 figure3:**
[figure not shown]
Screenshot of the to-do list for patients in the Listeo+ app.

Once the app is downloaded, patients will be able to use a personalized QR code included in their printed recommendations that will allow them to access their episode identification data and their personalized recommendations already set up by their anesthesiologist in the Web-based Listeo+ module integrated into the EHR platform of the Hospitals (Figure 4). Simultaneously, the EHR also sends all the necessary data for the app via Web service establishing the communication between the EHR and the app for the very first time.

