## Results

Currently, this study is in the recruitment phase, which will end once 790 patients are included (395 for each arm). The data collection and cleaning phases are estimated to be completed in April 2019, and the analysis with the final results will be conducted in July 2019.

Previously, the technical aspects of interoperability between the hospital and the Listeo+ app backend (set of system components accessible only to the developers or platform administrators) were resolved successfully, defining an application programming interface for Web services. In December 2016, an eCRF was created that was fully integrated into the EHR of the participating centers.

Prior to the recruitment of patients, a pilot phase was conducted in January 2017 with the aim of identifying complications in the subsequent phases of recruitment and data analysis. During the pilot phase, face-to-face sessions were held in the hospitals with both health professionals and specialized information and communication technologies personnel. In these sessions, test runs were performed with several patients, verifying the effective communication between the systems and the usability of the new functionality integrated into the EHR. As a result, a telephone call was included in the protocol, at 7 and 14 days after the provision of recommendations during the anesthesiologist appointment, for the patients of the intervention group who had not downloaded their personal preoperative recommendations using the QR code. In addition, two new recommendations were added (see Multimedia Appendix 2: R1_18 and R3_24), and the wording of the recommendations was modified to facilitate patient understanding. Simultaneously, improvements were made in the design and functionality of Listeo+.

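### As written, type 2 recommendations are scored at the visit where the recommendation list and app code are handed over, so they cannot respond to the app, yet they count in the primary percentage

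*Protocol article*

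**What the plan says.** All statements are in the protocol article.

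- **Primary Outcomes.** The outcome is one percentage over the recommendations: "The primary outcome will be measured as the average percentage of patient compliance with preoperative recommendations". Scoring times differ by type. For type 2: "Compliance with type 2 recommendations will be checked at the point of anesthesia consultation". For the others: "whereas types 1 and 3 at the point of patient reception and preparation the day of surgery". No type is set aside.
- **Participants.** There are three visits: surgery consultation, anesthesia consultation, and admission for the operation. The anesthesia consultation is described once, as a face-to-face visit for "all patients except for ophthalmological patients with indication for topical anesthesia".
- **Results.** The pilot led to telephone calls to intervention patients who had not downloaded their recommendations, timed "at 7 and 14 days after the provision of recommendations during the anesthesiologist appointment".
- **Intervention (text after Figure 3).** After download, patients "use a personalized QR code included in their printed recommendations" to reach "their personalized recommendations already set up by their anesthesiologist in the Web-based Listeo+ module".
- **Exclusion Criteria.** A rescue call goes to patients who, "within 7-14 days, have not registered on the Listeo+ app", with a further 72 hours allowed after the call.

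The content and number of type 2 items are in Multimedia Appendix 2, and the patient flow is in Figure 1. Neither is shown.

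**The concern.** An outcome item can show an effect of the app only if it is scored after the patient could have used the app. If type 2 compliance is recorded at the appointment where the list and its code are handed over, the two arms have had the same care up to that moment. Among all randomized patients, the expected difference on those items is then zero. Averaging them with types 1 and 3 shrinks the overall difference in proportion to the type 2 share. A real effect on the responsive items becomes harder to detect, and the reported estimate understates it.

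A smaller point concerns ophthalmology patients under topical anesthesia. They have no anesthesia consultation, and no other checking point for type 2 is given. The article does not say whether type 2 items are left out of their denominator.

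**Working it through.** **Order of events in the text**

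| Event | When | Section |
|---|---|---|
| App content set up by the anesthesiologist | Before the patient can open it | Intervention |
| Recommendations provided, from which the 7- and 14-day calls are counted | Anesthesia appointment | Results |
| App opened with the code on the printed list | After the list is in hand | Intervention |
| Type 2 scored | Anesthesia consultation | Primary Outcomes |
| Registration still awaited | Up to 7–14 days, plus 72 hours after the call | Exclusion Criteria |
| Types 1 and 3 scored | Day of surgery | Primary Outcomes |

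With a single anesthesia visit, the second and fourth rows fall on the same occasion, and app use comes later.

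**The plan's own sample size.** Sample Size and Statistical Plan gives alpha .05, beta .2, a 10-point difference in proportions and 395 per group. It states neither the control rate nor whether the test is one- or two-sided. With p̄ the mean of p1 and p2, the two-sided pooled formula is

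n = [1.960·√(2p̄(1−p̄)) + 0.8416·√(p1(1−p1) + p2(1−p2))]² / (p2−p1)²

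- 50% vs 60%: (1.3790 + 0.5891)² / 0.01 = 387.3, so 388.
- 45% vs 55%: (1.3859 + 0.5921)² / 0.01 = 391.3, so 392.
- Variance set to its maximum in both terms: 393.

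All are within 3% of 395. The plan's figure is therefore consistent with rates near 50%, and its arithmetic is not in question.

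**Dilution.** Let w be the share of type 2 items, Δ the effect on types 1 and 3, and zero the effect on type 2. Then

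overall difference = (1−w)·Δ + w·0 = (1−w)·Δ.

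Three inputs are assumptions: w = 10, 20 or 30%; Δ = 10 points on types 1 and 3 only; control rate 50%. With d the overall difference, p1 = 0.5, p2 = 0.5 + d and n = 395 per arm,

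power = Φ{ [d·√n − 1.960·√(2p̄(1−p̄))] / √(p1(1−p1) + p2(1−p2)) }, with √395 = 19.875.

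| w | d | Inside Φ | Power |
|---|---|---|---|
| 0 | 0.10 | (1.9875 − 1.3790)/0.7000 = 0.869 | 80.8% |
| 10% | 0.09 | (1.7887 − 1.3803)/0.7014 = 0.582 | 72.0% |
| 20% | 0.08 | (1.5900 − 1.3815)/0.7026 = 0.297 | 61.7% |
| 30% | 0.07 | (1.3912 − 1.3825)/0.7036 = 0.012 | 50.5% |

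At an assumed control rate of 70%, the same steps give 90.2, 82.8, 72.8 and 60.6%. The level is higher, but the loss remains.

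These figures use the two-proportion scale of the plan's own calculation. The outcome as defined is a mean percentage per patient, so they illustrate the direction and order of the loss and are not the power of that endpoint.

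**The case against.** The strongest objection is that the deciding facts are not shown. Items checked at the anesthesia consultation would naturally be items to be met by then, and so issued earlier, perhaps at the surgery consultation. The Intervention section says who sets up the app content, not at which visit. The only dated statement is a clause in the Results section about follow-up calls, and it does not say that every type is first issued there. Topical-anesthesia ophthalmology patients must receive their list somewhere else. The Allocation section lists anesthetic evaluation among data collected after allocation, which fits entry before that visit.

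This stands as a limit on certainty. A reader might infer that type 2 items are known to be insensitive to the app. The article does not support that, because Appendix 2 or Figure 1 could show otherwise. The objection does not remove the conflict, however. For type 2 to respond, the app itself must be open before the check, not just the paper advice issued. No section says so, and the sections on set-up and provision point the other way.

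A reader might also infer that the trial is underpowered, with power as low as about 50%. That is not supported either. The type 2 share is unknown, the control rate is not stated, and the planned 10 points is not split by type. If it is already the difference expected over all items, no further dilution applies.

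Finally, a reader might see the ophthalmology exemption as biasing the comparison. It does not, since it applies to both randomized arms. The Relevance of the Study section says lists are selected by patient characteristics, so type 2 items may simply be absent for these patients.

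**Conclusion.** The point holds on the text as written: with one anesthesia consultation, type 2 items are scored at the visit where the list and app code are provided, and they remain in the primary percentage. On that reading they have no expected between-arm difference, and they shrink the overall effect by the factor (1−w).

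The size cannot be known from the article. The fall from 80.8% to 72.0, 61.7 or 50.5% is conditional on type 2 shares of 10, 20 or 30%, a 50% control rate, and the 10 points applying to types 1 and 3 only. The effect is loss of sensitivity, not a false positive. The denominator for patients without an anesthesia visit is a secondary detail. Confidence is medium, because the appendix and the flowchart could show that app access comes earlier.

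**What to change.** 1. Reconcile Primary Outcomes, Participants, Intervention and Results: state at which visit type 2 items are issued and at which visit the app can first be opened.
2. Unless app access precedes the type 2 check, base the primary percentage in both arms on items scored after access, that is types 1 and 3 on the day of surgery. Report type 2 compliance separately. If the 10 points then refers to those items, 395 per group still gives about 80% power under the near-50% assumption.
3. If app access does precede the check, correct the Intervention and Results text, keep type 2 in the percentage, and count it only for patients who attend the anesthesia visit.

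The cost is small. Type 2 is already checked at a separate point, so this changes the wording of the outcome definition and needs no new data. The downside of step 2 is that the primary outcome covers fewer items. Because recruitment is under way, settle step 1 from the appendix and flowchart first, so that items the app can influence are not dropped. Record the change as one made on timing grounds, without reference to results by arm.

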#### Secondary Outcomes

The secondary outcomes include the rate of surgery cancellations (the absolute number of cancellations compared with the number of scheduled operations for each study group in the study period) and the associated consumption of hospital resources assessed by a cost analysis between the control and intervention groups, so only direct costs will be considered. To evaluate the user experience with the Listeo+ app in the intervention group, the perceived usability and utility of mHealth apps will be analyzed. The level of usability, defined as the extent to which Listeo+ is utilized by users to achieve specific objectives of mHealth apps [36], will be evaluated exclusively in patients, whereas the perceived utility of Listeo+ will be evaluated in health professionals using qualitative techniques.

Then, the absolute change (numerical difference over the two study groups) and relative change (percentage of variation among the intervention group over the SOC) will be determined to assess the impact of the intervention for the primary and secondary outcomes (except for variables related to user experience and the level of usability).

### Participants

Figure 1 presents the patient flow from the MAS assessment appointment to hospital discharge. This includes a first visit to surgery consultation, a second face-to-face anesthesia consultation (all patients except for ophthalmological patients with indication for topical anesthesia), and a third hospitalization visit to undergo MAS. Patients in the control group will follow the existing MAS patient assistance route in the centers, which consists of providing written recommendations. Participants are not going to pay for the app.

### Intervention

Patients included in the intervention group will be provided with personal recommendations through the Listeo+ mobile app (Figures 2 and 3). These personal recommendations will also be printed and provided to the intervention group. Furthermore, the intervention group patients will be given access to download the mobile app through their mobile apps market (Google Play and Apple Store) using a link and quick response (QR)code.

**Figure 1 figure1:**
[figure not shown]
Patient flowchart. MAS: major ambulatory surgery.

**Figure 2 figure2:**
[figure not shown]
Screenshots of Listeo+ app.

**Figure 3 figure3:**
[figure not shown]
Screenshot of the to-do list for patients in the Listeo+ app.

Once the app is downloaded, patients will be able to use a personalized QR code included in their printed recommendations that will allow them to access their episode identification data and their personalized recommendations already set up by their anesthesiologist in the Web-based Listeo+ module integrated into the EHR platform of the Hospitals (Figure 4). Simultaneously, the EHR also sends all the necessary data for the app via Web service establishing the communication between the EHR and the app for the very first time.

**Figure 4 figure4:**
[figure not shown]
Screenshot of health care professionals’ Listeo+ module within the electronic health record platform.

Any interaction between app users and individualized recommendations will be immediately notified to the Listeo+ module and visualized in the EHR platform, which will automatically send notifications to the mobile app as well as emails to the designated health care professional of the participating center in case a critical recommendation (recommendations that may pose a risk to the patient or in which patient noncompliance may lead to the suspension, cancellation, or rescheduling of surgery as stated in Multimedia Appendix 2) is not marked. Additionally, health care professionals will be able to contact by phone to encourage patients to meet the recommendation or solve any potential problem. Notably, the nature of the incident will always be registered.

### Sample Size and Statistical Plan

The sample size required to estimate the main objective of this study was calculated as 395 patients per group for a total of 790 patients. This estimate was made assuming an alpha risk of .05, a beta risk of .2, and a difference in proportions between the groups of 10%. The analysis will be performed considering per intention-to-treat (ITT) and per protocol populations. The ITT population will include all randomized patients, whereas the per protocol population will include randomized patients who finally obtain an appointment to undergo MAS.

In addition, statistical analyses will be performed using the R software version 3.3.2 (R Foundation for Statistical Computing). For all analyses, an alpha risk of .05 will be assumed; therefore, to consider a statistically significant difference, the *P* value of the contrast statistic should be ≤.05. The statistical analysis planned *a priori* will consist of a descriptive analysis of the demographic and clinical characteristics of patients. For quantitative variables, the mean, SD, 95% CIs, variance, SE, 5% trimmed mean, median, minimum, and maximum will be calculated. For qualitative variables, frequency distributions with their respective percentages will be calculated. To determine whether there are differences in the level of compliance with surgical recommendations between the group with written recommendations and the group with written recommendations plus the app, Fisher's exact test will be performed.

To assess the influence of sociodemographic and clinical characteristics of patients in the level of compliance with preoperative recommendations, multivariate logistic regression will be performed. Furthermore, the reasons for the exclusion of the ITT population will be included.

### Allocation

Patients who meet the inclusion criteria and sign informed consent will be provided with an information sheet about the project and evaluated before participating in the study. To allocate patients to study groups, simple randomization 1:1 procedure will be used. To include patients in the study, each center will be provided with one randomization scheme generated by computer. Given the characteristics of the study, it is not possible to blind patients and professionals. Subsequently, we will collect sociodemographic data (age, sex, area of residence of patients, level of education of patients or caregivers using the app or patient or caregiver of the control group, occupation, marital status, and knowledge or handling of apps), clinical data (type of surgery, medical diagnosis [International Classification of Diseases, Ninth Revision], anesthetic evaluation, and medications taken), and functional situation by measuring disability (Barthel index).

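### The primary comparison is an unadjusted Fisher's test in a four-centre, multi-specialty trial: valid, but it gives up precision; and simple randomisation does not secure the stated 395 per arm

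*Protocol article*

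**What the plan says.** All places are in the Protocol article.

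- **Allocation:** "To allocate patients to study groups, simple randomization 1:1 procedure will be used". The same section adds that "each center will be provided with one randomization scheme generated by computer". No blocks or strata are mentioned. Type of surgery is among the clinical data collected.
- **Sample Size and Statistical Plan:** the sample size was "calculated as 395 patients per group for a total of 790 patients", "assuming an alpha risk of .05, a beta risk of .2, and a difference in proportions between the groups of 10" per cent. For the difference in compliance between the arms, a Fisher's "exact test will be performed". A multivariate logistic regression follows. Its stated purpose is to assess how patients' sociodemographic and clinical characteristics influence compliance, and centre is not named in it.
- **Eligibility Criteria, Participants and Primary Outcomes:** patients come from traumatology, orthopaedic surgery, ophthalmology or general surgery. Ophthalmology patients due topical anaesthesia do not attend the anaesthesia consultation, which is where type 2 recommendations are checked.
- **Results:** the recruitment phase is one "which will end once 790 patients are included (395 for each arm".

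**The concern.** Centre and specialty are plausible sources of variation in compliance. For some ophthalmology patients the visit at which part of the outcome is checked does not take place, so specialty may also affect how the outcome is measured. Simple randomisation does not balance either factor, and the named primary test does not account for either. At stake are some power and protection against a chance imbalance that would be awkward to explain afterwards.

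The second matter is one of consistency. A method that leaves arm sizes to chance is paired with a recruitment end point written as an exact number per arm.

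**Working it through.** **Inputs.** From the article: 395 per group, 790 in total, alpha 0.05, beta 0.2, a 10-point difference, 1:1 simple randomisation, four centres. Assumed because the article does not give them: a two-sided test, a baseline near 45 to 50%, equal centre sizes, and the centre-specific rates below. Compliance is treated as binary, as the sample size and Fisher's test imply.

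**1. The plan's own figure.** For 45% v 55%:

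n = [1.96 × √(2 × 0.5 × 0.5) + 0.8416 × √(0.45 × 0.55 + 0.55 × 0.45)]² / 0.10² = 391.3, so 392 per group.

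The maximum-variance form gives 0.5 × (1.96 + 0.8416)² / 0.01 = 392.4, and 50% v 60% gives 388. The stated 395 is reproduced to within 2%.

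**2. Arm sizes under simple randomisation.** One arm is Binomial(790, 0.5).

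- SD = √(790/4) = 14.05; 95% range 367 to 423.
- P(exactly 395/395) = 0.0284, close to √(2/(π × 790)).

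Power at 45% v 55%, with p̄ the pooled proportion:

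Φ{[0.10 − 1.96 × √(p̄(1 − p̄)(1/n₁ + 1/n₂))] / √(0.2475 × (1/n₁ + 1/n₂))}

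| Split | Power |
|---|---|
| 395 / 395 | 80.4% |
| 381 / 409 | 80.3% |
| 367 / 423 | 80.2% |
| 355 / 435 | 80.0% |

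The loss at the 95% limit is 80.4 − 80.2 = 0.2 points.

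**3. Balance within a centre.** 790/4 is about 198. The SD of one arm is √(198/4) = 7.0, and the 95% range is 85 to 113. In a centre-by-specialty cell of 50 (illustrative) it is 18 to 32.

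**4. What ignoring centre costs.** Simulated trials of 790 (3,000 per row), four equally likely centres, simple randomisation, 10-point effect. Fisher's test is compared with a centre-stratified Mantel-Haenszel test.

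| Assumed control rates by centre | Power, Fisher | Power, stratified | Type I error, Fisher | Type I error, stratified |
|---|---|---|---|---|
| 45% in all | 80.2% | 81.0% | 4.7% | 5.1% |
| 35, 40, 50, 55% | 79.8% | 81.8% | 4.3% | 4.7% |
| 25, 35, 55, 65% | 79.2% | 84.4% | 4.9% | 5.5% |

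The simulation standard error is about √(0.8 × 0.2/3000) = 0.7 points for power and √(0.05 × 0.95/3000) = 0.4 points for type I error. The gain of about 1 point in the first row arises with no centre differences at all. It therefore reflects the conservatism of Fisher's test and simulation noise, not centre.

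**5. Analytic cross-check of the widest scenario.**

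- Between-centre variance = (0.20² + 0.10² + 0.10² + 0.20²)/4 = 0.025.
- Total variance = 0.45 × 0.55 = 0.2475.
- SE of the difference, centre ignored: √(2 × 0.2475/395) = 3.54 points.
- SE of the difference, centre removed: √(2 × 0.2225/395) = 3.36 points.
- Chance centre imbalance alone moves the estimated difference with SD √(2 × 0.025/395) = 1.1 points.
- Approximate power: Φ(10/3.54 − 1.96), about 81%, against Φ(10/3.36 − 1.96), about 85%, in line with the last row.

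**The case against.** The strongest reply is that an unadjusted test is valid under simple randomisation and that covariates are usually settled in the analysis plan. The first part stands: Fisher's type I error was 4.3 to 4.9% throughout. The second stands in part. An analysis plan not shown may add an adjusted analysis, but this article does name the unadjusted test for the treatment comparison. The logistic regression is only a partial answer. It may include type of surgery, but it is framed as a study of influences on compliance and does not name centre.

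A reader might infer more than the article supports:

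- **That 395 per arm cannot be reached.** It can; it is merely unlikely. If 395 were a minimum in both arms, simulated recruitment would need a median of 808 patients (95th percentile 847). The plainer reading is 790 in total, with 395 as the planned split.
- **That one arm will be closed once full, making later allocations predictable and tied to calendar time.** The article nowhere says this.
- **That concealment is weak because each centre receives a scheme.** The article does not say who holds it or how it is released, and a condensed article may leave that to the full protocol. Simple randomisation is itself the least predictable method. A switch to permuted blocks during open-label recruitment would trade away some of that unpredictability for about 0.2 points of power.
- **That adjustment is worth 11 to 25% more patients.** This requires centre and specialty to explain 10 to 20% of the variance (1/0.90 = 1.11; 1/0.80 = 1.25). Nothing in the article supports that share. For centre alone, even the 40-point spread in the widest scenario gives 0.025/0.2475, about 10%.
- **That recommendation lists differ by specialty.** The article says they are tailored to the patient. It documents only a different visit route for some ophthalmology patients.

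**Conclusion.** The primary comparison is valid but less precise than it could be at almost no cost. With equal centres and the assumed centre rates, the stratified test gains about 1 to 5 points of power. About 1 point of that appears even when the centres do not differ, so the part due to centre runs from nothing to roughly 4 points. The gain from specialty is not quantified, because the article gives no figures for it. The different route for some ophthalmology patients is a further reason to include it. Omitting these factors is a loss of efficiency and of protection against chance imbalance, not an error in the test.

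The mismatch between the Allocation and Results sections is real and minor. The 395 per arm is an expectation under the stated method, and departures within the 95% range leave power at about 80%.

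**What to change.** - Make the primary treatment comparison one that adjusts for centre and specialty: for example a regression with treatment, centre and type of surgery, or, for centre alone, a centre-stratified Mantel-Haenszel test. Report the adjusted difference in proportions as well as any odds ratio, since the trial was sized on a 10-point difference. Keep Fisher's exact test as a sensitivity analysis.
- Leave the allocation method as it is. In the Results section, say that recruitment ends at 790 patients in total, with 395 as the expected number per arm.

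The cost is one analysis change and one sentence. Type of surgery is already collected and the centre of each patient is known, so no new data are needed. Sparse centre-by-specialty cells argue for main effects only. The abstract mentions an intermediate analysis 10 months into recruitment, so the amendment should be dated and should state whether results by arm had been seen.
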